#### Secondary outcome measure

2.Postoperative bile reflux in the esophagus. The endoscopic finding of postoperative bile reflux in the esophagus. Mild bile reflux (BR) was assessed if the biliary reflux was asymptomatic and detected only by an endoscopic picture of gastritis near the gastroenteroanastomosis. A grade of average BR was assessed by the presence of pain or total gastritis of the pouch caused by the presence of bile. A grade of severe BR was assessed if BR symptoms of stomach pain or heartburn were intolerable or by endoscopic verification of esophagitis by the presence of bile in the esophagus [15]. Time frame: at 12, 24, and 36 months after surgery.3.Assessment of GERD if preoperative GERD symptoms (GERD-HRQL) were present or if GERD symptoms occurred postoperatively (de novo GERD).

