**Methods:**

The study was designed as a single-center prospective, interventional, randomized controlled trial. Masking: None (open label). Allocation: randomized. Enrollment: 100 obese patients. The relevant ethics committee approved the trial protocol.

The endpoints (body mass index, bile reflux in the esophagus, other reflux symptoms) will be assessed presurgery and postsurgery (12, 24, and 36 months postoperatively).

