### Objectives {7}

We hypothesize that total fundoplication can not only treat GERD but also significantly prevent the return of weight, such as after banded gastric bypass, prevent postoperative bile reflux in the esophagus, and decrease de novo GERD.

The aim of this article is to describe the design and protocol of a randomized controlled trial comparing the outcomes of two methods of LOAGB: the experimental method with wrapping versus the standard method nonwrapping fundus of the excluded part of the stomach.

The main aim of the study are as follows:
Comparing the primary outcome measure: change in body mass index in both groups and weight regain.Comparing the secondary outcome measures: postoperative bile reflux in the esophagus; assessment of GERD if preoperative GERD symptoms (GERD-HRQL) were present or if GERD symptoms occurred postoperatively (de Novo GERD).

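### Secondary outcome 2 is named as an endoscopic finding of bile in the esophagus, but only one of its four grading routes requires such a finding

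*Protocol article*

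**What the plan says.** All references are to the Protocol article.

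The Objectives section states the hypothesis that the wrap will, among other things, "prevent postoperative bile reflux in the esophagus". The section on secondary outcome measures gives the outcome that name and describes it as "The endoscopic finding of postoperative bile reflux in the esophagus", assessed at 12, 24 and 36 months. Three grades follow, with a literature source cited for them:

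- **Mild:** the reflux causes no symptoms and is "detected only by an endoscopic picture of gastritis near the gastroenteroanastomosis".
- **Average:** "A grade of average BR was assessed by the presence of pain or total gastritis of the pouch caused by the presence of bile".
- **Severe:** "BR symptoms of stomach pain or heartburn were intolerable or by endoscopic verification of esophagitis by the presence of bile in the esophagus".

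The assessment rows of Table 1 carry the esophageal name at the same three visits. The Discussion, describing the same outcome, speaks only of biliary reflux and gives no location. The trial is open label (Trial design; Who will be blinded).

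**The concern.** The name of the outcome and its criteria point to different parts of the anatomy. The name makes a claim about the esophagus. The criteria mostly concern the tissue near the anastomosis, the pouch, and what the patient feels.

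This matters because the esophageal claim is one of the trial's hypotheses, and the Abstract presents bile reaching the esophagus as what negates the benefit of the standard operation. If the groups are compared on the grade and the result is reported under the outcome's name, two errors are possible. A difference in pain or pouch gastritis could be presented as protection of the esophagus. Conversely, a real esophageal difference could be diluted by cases graded on findings elsewhere. Patients know their operation, so the routes that rest on symptoms are also open to reporting bias. The endoscopic route is less exposed to this.

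**Working it through.** **Step 1. Does each route require what the name claims?** The three grades contain four routes, because severe has two branches.

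| Route | Criterion, in summary | Esophageal finding? | Can symptoms alone meet it? |
|---|---|---|---|
| Mild | No symptoms; gastritis near the anastomosis is the only finding | Excluded by the wording | No |
| Average | Pain, or gastritis of the whole pouch due to bile | Not required, not excluded | Yes, through pain |
| Severe, symptom branch | Intolerable stomach pain or heartburn | Not required, not excluded | Yes |
| Severe, endoscopic branch | Esophagitis with bile in the esophagus | Required | No |

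One route of four requires an esophageal finding, one excludes it and two leave it open. If the two criteria for average are counted apart, the tally is one of five; the conclusion is the same.

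**Step 2. Is the mismatch settled elsewhere?** Objectives and Table 1 repeat the esophageal name. The Discussion drops the location. Nowhere does the article say that only the endoscopic branch of severe carries the esophageal claim, or that the grade stands beside a separate yes/no finding.

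**Step 3. Illustration of dilution, under assumed rates.** The article states no expected rate or power for this outcome, so there is no figure to reproduce. Inputs from the document: 50 patients per group (Recruitment), and chi-square or Fisher's exact test at 0.05 (Statistical methods). Assumptions: esophageal bile reflux in 10% of controls and 0% with the wrap. The 10% borrows the top of the 0.6–10% range in the Background, which concerns reflux resistant to medical treatment.

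- *Esophageal finding alone.* With no event in the wrap group, Fisher's two-sided p is 2 × C(50,k)/C(100,k). This is 0.056 for k = 5 and 0.027 for k = 6, so at least six control events are needed. Power = P(Bin(50, 0.10) ≥ 6) = 38.4%.
- *Any grade counts, with non-esophageal cases added equally in both groups.* If a fraction q qualifies by another route, independently of esophageal bile, the control rate is 0.10 + 0.90q and the wrap rate is q. The share of control cases that are esophageal is 0.10/(0.10 + 0.90q).

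| q | Control vs wrap | Exact Fisher power | Esophageal share, controls |
|---|---|---|---|
| 0 | 10% vs 0% | 38.4% | 100% |
| 0.1 | 19% vs 10% | 16.0% | 53% |
| 0.2 | 28% vs 20% | 10.9% | 36% |
| 0.3 | 37% vs 30% | 7.8% | 27% |

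If the added 20% does not overlap with the esophageal cases (30% vs 20%), power is 15.5%. The direction is the same in every row, but the size depends on q and on the overlap, and the document supplies neither.

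**The case against.** **Every grade presupposes bile reflux.** Mild is a form of asymptomatic biliary reflux, severe speaks of symptoms of bile reflux, and in the average grade the reference to bile as the cause may qualify the pain as well as the gastritis. Bare pain is therefore not clearly enough. This stands as far as it goes: it would be wrong to infer that the average grade and the symptom branch of severe consist of patients without bile in the esophagus. They can include such patients; only mild excludes an esophageal finding. But bile reflux into the pouch is not bile in the esophagus, so the mismatch remains.

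**The opening sentence may be the outcome and the grade only a cited scale beside it.** This reading is possible, and the cited source is not at hand. The text does not say so, however, and the grades are the only working criteria given. How grades are combined for analysis may properly be left to an analysis plan. The point here does not rest on that omission but on criteria that the article states and that do not fit the name.

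**The schedule.** A reader might infer a second contradiction, because the Abstract says that the endpoints "will be assessed presurgery and postsurgery" while Table 1 has no preoperative entry for bile reflux. The documents do not support making this a defect. The Abstract sentence covers three endpoints together, and Table 1 does schedule body mass index and GERD symptoms before surgery. The third is named as postoperative, and the mild criterion and the pouch-gastritis criterion need an anastomosis or a pouch that does not exist before surgery.

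**The power loss.** A reader might take the fall from 38% to 16% or lower as a property of this trial. It is not. The added rates are assumed, and equal addition presumes that the wrap has no effect on pouch findings or symptoms.

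**Renaming alone would do.** Calling the outcome biliary reflux throughout, as the Discussion does, would remove the inconsistency. It would also leave the esophageal hypothesis in Objectives without an outcome that measures it.

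**Conclusion.** The concern holds as a mismatch between the name and the criteria of a secondary outcome. One of four grading routes requires an esophageal finding. The mild grade is the clearest conflict, since its wording confines the finding to the area near the anastomosis. A difference in grade would not by itself support a statement about bile in the esophagus.

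This conclusion follows from the text and needs no assumed rate. Its numerical effect is unknown; the power figures show only the direction of dilution. The matter deserves correction before analysis, but it touches a secondary outcome and does not affect the body mass index comparison.

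**What to change.** 1. At the 12-, 24- and 36-month endoscopies that the outcome already implies, record and analyse bile in the esophagus or bile-related esophagitis as yes/no. Let this outcome alone carry the esophageal name.
2. Keep the mild, average and severe grade, but report it separately as biliary reflux of the pouch and symptoms.
3. Align the naming in Objectives, the secondary outcome measures, Table 1 and the Discussion.

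**Cost.** The data need one added item on the case report form and no further procedure. Trial status reports that recruitment began on 29 March 2021, so the change is an amendment, with written notice to participants and the ethics committee as the protocol's own section on amendments provides.

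The scientific price is scarcity of events. At 10% the control group would yield about 50 × 0.10 = 5 esophageal events. At 0.6%, the lower end of the Background range for treatment-resistant reflux, it would yield 50 × 0.006 = 0.3, and power would be essentially nil. The comparison will be imprecise and should be reported as an estimate with its interval. That imprecision is a fair statement of what 50 per group can show about the esophagus; the broader grade does not remedy it, because it answers a different question.

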**Assessments:**						
**Body mass index**	X	X	X	X	X	
**Change of body mass index**			X	X	X	
**Postoperative bile reflux in the esophagus**			X	X	X	
**GERD symptoms** or postoperative de novo GERD symptoms	X	X	X	X	X	
**Statistical analysis**						X

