Simultaneously, secondary outcome measures were the likelihood of biliary reflux within 12, 24, and 36 months after this procedure. Finally, GERD will be assessed if preoperative GERD symptoms are present or if GERD symptoms occur postoperatively (de novo GERD). For this aim, we will use a quality-of-life scale for gastroesophageal reflux disease (GERD-HRQL) [20].

In the present randomized controlled trial, we expect to show that one anastomosis gastric bypass with fundoplication ring for obese patients will better prevent the return of weight and bile reflux than the standard method. The idea to investigate in a randomized study the combination of two procedures as a primary procedure for one-anastomotic gastric bypass was expressed by [name] [13, 21].

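### The article disagrees with itself on who is assessed for GERD; if the symptom-conditional wording is followed, GERD-HRQL scores come from a set partly selected after randomisation

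*Protocol article*

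**What the plan says.** Three places in the protocol article attach a condition to the GERD outcome.

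- Outcomes {12}, secondary outcome measure, item 3: "Assessment of GERD if preoperative GERD symptoms (GERD-HRQL) were present or if GERD symptoms occurred postoperatively (de novo GERD").
- Objectives {7}, in nearly the same words: "assessment of GERD if preoperative GERD symptoms (GERD-HRQL) were present or if GERD symptoms occurred postoperatively (de Novo GERD").
- Discussion: "GERD will be assessed if preoperative GERD symptoms are present or if GERD symptoms occur postoperatively (de novo GERD"). The next sentence supplies the instrument: "we will use a quality-of-life scale for gastroesophageal reflux disease (GERD-HRQL").

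Two places carry no such condition.

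- Table 1, Assessments, has a row for GERD symptoms "or postoperative de novo GERD symptoms", marked at all five visits from V1 (preoperative) to V5 (36 months).
- Abstract, Methods: "The endpoints (body mass index, bile reflux in the esophagus, other reflux symptoms) will be assessed presurgery and postsurgery", with the postoperative times given as 12, 24 and 36 months.

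Objectives {7} also states the hypothesis that total fundoplication will "decrease de novo GERD". Statistical methods {20a} assigns one-way ANOVA to quantitative variables and chi-square or Fisher's exact test to qualitative ones. Section {20c} states intention-to-treat in general terms, for cases of nonadherence. The article gives no denominator, analysis set or metric specific to GERD.

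**The concern.** The condition has two limbs. Preoperative symptoms are a baseline characteristic, so restricting to those patients gives an ordinary baseline subgroup in which the randomised comparison is preserved. Postoperative symptoms arise after randomisation, and the trial's own hypothesis is that the wrap makes them rarer. If only patients meeting either limb complete the GERD-HRQL, a working wrap changes how many patients, and which kind, are scored in its arm.

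Suppose de novo cases are milder than pre-existing ones. Preventing them then removes low scores from the wrap arm and raises its mean among those scored. An ANOVA on those scores would compare two differently selected groups. The intention-to-treat statement cannot repair this, because scores never collected from symptom-free patients cannot be analysed. The trial is also open label, so reporting of the triggering symptom may depend on knowing the arm. That weakness is shared by any patient-reported outcome in an unblinded trial, but a symptom trigger lets it affect who is scored as well as what they score.

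What is at stake is the interpretation of a secondary outcome tied directly to the trial's hypothesis. The primary outcome, BMI change, is not touched.

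**Working it through.** **The plan's own figures.** The article gives no GERD rate, score or sample size, so there is no GERD figure to reproduce. Its only sample-size result concerns BMI and does reproduce from the stated constants: 2 × (1.96 + 1.28)² × 10² / 15² = 9.33 per group. It does not bear on this point.

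**Step 1: who is assessed.**

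| Place | Condition on symptoms? |
|---|---|
| Objectives {7} | Yes |
| Outcomes {12}, item 3 | Yes |
| Discussion | Yes, followed by the GERD-HRQL |
| Table 1, Assessments | No; V1 to V5 all marked |
| Abstract, Methods | No; before and after surgery |

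Staff working from the outcome definition and staff working from Table 1 could collect different data.

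**Step 2: what follows if the condition is applied.** The only input from the article is 50 patients per arm. The rest is assumed: 10 per arm have preoperative GERD, with mean postoperative score 14 (standard) and 12 (wrap). Of the other 40 per arm, 15 (standard) and 2 (wrap) develop de novo GERD with mean score 7. Symptom-free patients score 0.

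Mean among those scored = (sum of scores) / (number with preoperative or de novo symptoms):

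- Standard: (10 × 14 + 15 × 7) / 25 = 245 / 25 = 9.80
- Wrap: (10 × 12 + 2 × 7) / 12 = 134 / 12 = 11.17
- Difference, wrap minus standard: +1.37, so the wrap looks worse

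Mean in all randomised patients = (sum of scores) / 50:

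- Standard: 245 / 50 = 4.90
- Wrap: 134 / 50 = 2.68
- Difference: −2.22, so the wrap is better

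De novo proportion among those free of GERD at baseline: 15/40 against 2/40, which is in the right direction.

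**Step 3: how far this depends on the assumptions.** Two changes to the example, one at a time:

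- Wrap also clearly improves existing GERD (score 7 against 14): the scored-only means are 245 / 25 = 9.80 and (70 + 14) / 12 = 7.00. The difference is −2.80, with no reversal.
- De novo cases as severe as existing ones (score 14): the means are 350 / 25 = 14.00 and (120 + 28) / 12 = 12.33. The difference is −1.67, with no reversal. In all patients it is 350 / 50 = 7.00 against 148 / 50 = 2.96, or −4.04, so the scored-only figure understates the benefit.

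A grid of 4 × 4 × 4 = 64 scenarios used preoperative GERD of 10, 20, 30 or 40%; de novo rates (standard/wrap) of 10/2, 20/5, 30/5 or 40/10%; and a wrap score in existing GERD of 14, 12, 10 or 7 against 14 in the standard arm. The de novo score was 7 throughout. The wrap is better in all 64 when every patient is counted. Among scored patients only, it looks worse in 27:

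| Wrap score in existing GERD (standard 14) | Reversals |
|---|---|
| 14 (no effect) | 16 of 16 |
| 12 | 9 of 16 |
| 10 | 2 of 16 |
| 7 | 0 of 16 |

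Reversal therefore needs little wrap effect on existing GERD together with milder de novo cases.

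**The case against.** The strongest reply is that the conditional sentences may name two outcome categories, persistent and de novo GERD, and may not set a rule for who is asked. The Table 1 row pairs the same two categories and marks every visit. Establishing whether symptoms were present before or arose after surgery requires asking everyone. In Objectives {7} and Outcomes {12} the bracketed GERD-HRQL sits beside the preoperative symptoms, which fits use of the scale at baseline. None of the three sentences says that only symptomatic patients are assessed.

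A reader might go further than the documents allow and infer that GERD is definitely assessed only in symptomatic patients, that the arms will be compared on that selected group, and that a protective wrap will therefore look harmful. The documents do not support this. Table 1 and the abstract point the other way. No section confines the GERD analysis to symptomatic patients, and the hypothesis about de novo GERD concerns an incidence, for which chi-square or Fisher's test is available. The reversal depends on assumed inputs, and 37 of the 64 scenarios do not reverse. The inputs that most favour reversal give the wrap little or no effect on existing GERD, which sits badly with the trial's own hypothesis that fundoplication treats GERD.

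These points limit the claim but leave part of it standing. The conditional wording appears three times, including in the outcome definition itself, and in the Discussion it leads straight to the GERD-HRQL. Asking everyone about symptoms, as Table 1 may intend, is also not the same as scoring everyone on the scale. Defining the outcome is the protocol's task. A score cut-off for de novo GERD, by contrast, can reasonably be left to an analysis plan.

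**Conclusion.** The point holds as an inconsistency with a conditional consequence. The outcome definition, objectives and discussion make GERD assessment depend on symptoms; the schedule and abstract do not. If the conditional wording governs data collection, the GERD-HRQL comparison is not fully protected by randomisation. It can be biased and, where the wrap does little for existing GERD and de novo cases are milder, can point the wrong way (+1.37 among scored patients against −2.22 in all patients in the worked example). All rates and scores behind these figures are assumptions, so they show what is possible and do not predict the trial's result. If everyone is asked, as Table 1 suggests, the problem does not arise for the de novo proportion; if everyone also completes the scale, it does not arise for the score. The matter concerns a secondary outcome and is worth correcting mainly because doing so is cheap.

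**What to change.** Reword Objectives {7}, Outcomes {12} item 3 and the corresponding sentence in the Discussion to agree with Table 1, so that every randomised patient completes the GERD-HRQL at baseline and at 12, 24 and 36 months whatever their symptoms. State that scores are compared in all randomised patients, adjusted for the baseline score. State that de novo GERD is reported with all patients free of GERD at baseline as the denominator. The threshold that defines de novo GERD can be set in the analysis plan.

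The cost is one short questionnaire for symptom-free patients at visits already scheduled, plus the wording changes. Treatment and sample size are unchanged.

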#### Participant timeline {13}

The flow diagram of the study design is shown in Table 1.

**Table 1 Tab1:** The schedule of enrollment, interventions, and assessments of the FundoRingMGB trial

	Study period					
	Enrollment	Allocation	Post-allocation			Close-out
**Timepoint**	**V1 (preoperative)**	**V2 (operation)** ***March–December 2021***	**V3 12 months**	**V4 24 months**	**V5 36 months**	**April 2024**
**Enrolment:**						
**Eligibility screen**	X					
**Informed consent**	X					
**Allocation**		X				
**Interventions:**						
***[***FundoRingOAGB group***]***		X				
***[****L*OAGB group***]***		X				
**Assessments:**						
**Body mass index**	X	X	X	X	X	
**Change of body mass index**			X	X	X	
**Postoperative bile reflux in the esophagus**			X	X	X	
**GERD symptoms** or postoperative de novo GERD symptoms	X	X	X	X	X	
**Statistical analysis**						X

### Sample size {14}

Purpose sampling
Effect size (*d*) (postoperative change in BMI (%)) = 15%.SD = 10.

Formula for calculating sample size is:
$$ n=2\ \left( Z\alpha +Z\left[1-\beta \right]\right)2\times \mathrm{SD}2/\mathrm{d}2 $$

Level of significance = 5%, power = 80% (Sample size increases as power increases. Higher the power, lower the chance of missing a real effect), *Zα* = *Z* is constant set by convention according to accepted α error and *Z* (1-*β*) = *Z* is constant set by convention according to the power of study [16].

Sample size calculations in our study:
$$ \mathrm{Z}\alpha =1.96,\mathrm{Z}\ \left(1-\beta \right)=1.28,\mathrm{SD}=10,\mathrm{d}\ \left(\mathrm{effect}\ \mathrm{size}\right)=15 $$

*n* = 2 (1.96 +   1.28) 2 × 102/152 = 9.33 individuals in each group should be recruited in the study. However, we plan to include more than five times the number of patients in the sample.

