## Introduction

### Background and rationale {6a}

Typical early weight loss following bariatric surgery ranges from 47 to 80% of excess weight [1]. However, typical weight regain is 15–25% of that lost weight [2]. Weight regain after surgery is a major problem in bariatric practice. Therefore, adjustable bands and rings are used, such as “FobiRing” for banded gastric bypass [3]. However, foreign material can cause complications, such as erosion of the stomach wall [4]. Therefore, surgeons avoid the use of mechanical devices for banded gastric bypass.

Currently, laparoscopic one anastomosis gastric bypass (LOAGB) or minigastric bypass (MGB) is a common bariatric procedure for treating obesity [5]. The greatest criticism of the LOAGB is for the likelihood of biliary reflux [6]. Biliary reflux resistant to medical treatment has an incidence of 0.6–10% after one anastomosis gastric bypass and may be a reason for revisional surgery [7].

In addition, along with obesity, gastroesophageal reflux disease (GERD) is steadily increasing worldwide, and antireflux surgery must be performed simultaneously with bariatric surgery in obese patients [8]. In these cases, fundoplication may be performed using the fundus of the excluded part of the stomach [9]. Colpaert J et al. reported good short-term results with modified Nissen fundoplication for patients with reflux after RYGB [10]. They opted to perform the same procedure to slow down the passage of food through the gastric pouch. This procedure can be performed as a revision procedure after Roux-en-Y gastric bypass for the treatment of postoperative dumping syndrome [11].

In the literature, we did not find data on the use of a similar method for primary procedures and examples of use for patients without GERD to prevent biliary reflux in one anastomosis gastric bypass and de novo postoperative reflux esophagitis.

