### Recruitment {15}

We will sample a homogenous population group (obese patients with body mass index (BMI) from 30 to 50 kg/m^2^), thus reducing the standard deviation and hence the sample size. We will recruit 100 obese patients (50 patients in two groups).

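### The sample size section states 80% power but calculates with the 90% z-value, and its 15% effect is not defined as a between-arm difference on a named scale, so the fivefold margin has no clear meaning

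*Protocol article*

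**What the plan says.** Sample size {14} sets out the whole calculation. It gives "Level of significance = 5%, power = 80" per cent and describes the effect size as "postoperative change in BMI (%)) = 15" per cent, with an SD of 10. The formula is the usual one for two independent means. The values inserted are Zα = 1.96, Z(1-β) = 1.28, SD = 10 and d = 15, and the conclusion is that "9.33 individuals in each group should be recruited in the study". The section then says that over five times that number will be enrolled. Recruitment {15} fixes the number: "We will recruit 100 obese patients (50 patients in two groups").

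Three other sections bear on the effect size:

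- Background and rationale {6a} states "Typical early weight loss following bariatric surgery ranges from 47 to 80% of excess weight" and that "typical weight regain is 15–25% of that lost weight".
- Objectives {7} names prevention of weight regain as a main part of the hypothesis.
- Outcomes {12} lists BMI, change in BMI (kg/m²), excess BMI loss (EBMIL, %) and total weight loss (TWL, %) together under the primary outcome, at 12, 24 and 36 months, with 25 kg/m² as the reference for excess weight.

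**The concern.** Two inputs do not fit the calculation they are used in.

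**Power and z disagree.** A z of 1.28 belongs to 90% power and 0.84 to 80%. A reader cannot tell which power the sponsor intended, and the printed n does not belong to the printed power.

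**The effect is not the quantity the formula requires.** In a two-sample formula, d is the difference between the arm means. The label describes a change after surgery. By Intervention description {11a} both arms receive a one anastomosis bypass, so both will show such a change. The article does not say which of its primary measures d refers to, at which visit, or where 15 and 10 come from.

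This calculation is the only justification of the trial's size. The fivefold margin is measured against it, so if 15 is not a supported between-arm difference, the margin says little about how well the trial can answer its primary question.

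**Working it through.** **Inputs.** From Sample size {14}: α = 5% (two-sided, implied by 1.96), stated power 80%, z used 1.28, SD 10, d 15. From Recruitment {15}: 50 per arm. From Background and rationale {6a}: early loss 47–80% of excess weight, regain 15–25% of the loss. From Eligibility criteria {10}: BMI 30 to 50. From Outcomes {12}: reference BMI 25. Assumed: mean BMI 40 (midpoint of the eligible range; the article gives no mean) and no dropout unless stated.

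**Step 1. Reproduce the printed figure.** n = 2(Zα + Z(1-β))² SD²/d².

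- As printed: 2 × (1.96 + 1.28)² × 100/225 = 9.33, or 10 rounded up. Φ(1.28) = 0.900, so this is 90% power.
- At the stated 80%: 2 × (1.96 + 0.84)² × 100/225 = 6.97, or 7 rounded up.
- One-sided variants give 7.6 (90%) and 5.5 (80%). Only two-sided 5% with 90% power reproduces 9.33.

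**Step 2. Size of the margin as stated.** 50/9.33 = 5.4, or 50/10 = 5.0 against the rounded figure. If d really were a between-arm difference of 15 with SD 10, 50 per arm would give over 99.9% power.

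**Step 3. What the article's regain figures imply, as per cent of initial BMI.** If the wrap abolished all regain and did nothing else, the between-arm difference would be (BMI − 25)/BMI × share of excess lost × share regained.

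| Initial BMI | Excess, % of initial | Low (47%, 15%) | High (80%, 25%) |
|---|---|---|---|
| 30 | 16.7 | 1.2 | 3.3 |
| 40 | 37.5 | 2.6 | 7.5 |
| 50 | 50.0 | 3.5 | 10.0 |

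The middle case at BMI 40 (63.5% lost, 20% regained) is 37.5 × 0.635 × 0.20 = 4.8 points.

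**Step 4. The same figures on the EBMIL scale.** The excess factor drops out: 0.15 × 47 = 7.1 to 0.25 × 80 = 20 points. Here 15 lies inside the range.

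**Step 5. Power with 50 per arm, SD 10, two-sided 5% (two-sample t test).**

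| Between-arm difference | Power |
|---|---|
| 2.6 | about 25% |
| 4.8 | about 66% |
| 7.5 | about 96% |

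**Step 6. Detectable difference at 80% power.** By the normal formula, (1.96 + 0.84) × 10 × √(2/50) = 5.6; with the t distribution it is 5.7. With 40 evaluable per arm (20% loss, a figure not in the article), (1.96 + 0.84) × 10 × √(2/40) = 6.3.

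**The case against.** The strongest reply has four parts.

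- **The z slip is harmless in practice.** It raises the calculated n from 7 to 10 while enrolment stays at 50 per arm. This stands: no power is lost, and on its own it is a correction of wording.
- **The scale in Step 3 is the reviewer's choice.** Outcomes {12} puts EBMIL % and TWL % beside change in BMI, so a percentage effect is not foreign to the primary outcome, and on EBMIL 15 points is attainable. This also stands. It confirms that the scale of d has to be named.
- **The wrap need not act only through regain.** The endpoint is total BMI change, which includes initial loss. The background describes fundoplication used to slow the passage of food, and the hypothesis compares the wrap with banded bypass. The article's loss and regain figures are typical values, not upper limits. This stands too, although the article gives no between-arm figure for extra initial loss.
- **If the scale of d is undefined, so is that of the SD**, and the powers in Step 5 are conditional on SD 10 for per cent of initial BMI. Agreed; they are shown as conditional.

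A reader might therefore be tempted to conclude that 15 points is impossible on the article's own figures, or that the fivefold margin is illusory and the trial underpowered. The documents support neither. The 10-point ceiling needs both a particular scale and a regain-only mechanism, and 50 per arm still has about 96% power at 7.5 points.

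None of this answers the two faults themselves: the power and the z-value contradict each other, and d is not stated as a between-arm difference.

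**Conclusion.** The point holds in a limited form.

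- **Certain, without assumptions:** the stated 80% power and the z of 1.28 contradict each other. The printed 9.33 is the 90% figure, and 80% gives 6.97. The error is in the conservative direction.
- **Certain from the text:** d is labelled as a postoperative change, not as a difference between arms. Its measure, unit and time point are not fixed, and neither d nor the SD has a stated basis.
- **Conditional:** if d is per cent of initial BMI and the benefit comes only from preventing regain, the article's typical figures give 2.6 to 7.5 points at an assumed BMI of 40, and at most 10 at BMI 50. The fivefold margin is then measured against an unsupported effect. It vanishes for low and middle regain-sized effects (power about 25% and 66%) and shrinks at the upper end (96%). This assumes SD 10 and complete follow-up.

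The size of the trial is not shown to be wrong. What is wrong is its stated justification.

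**What to change.** Keep n = 100 and restate Sample size {14}:

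1. Make power and z agree, either 80% with 0.84 (6.97, so 7 per arm for the present inputs) or 90% with 1.28 (9.33, so 10 per arm).
2. Define d as the between-arm difference in one named primary measure, with its unit and time point, and give the basis for d and for the SD on that scale.
3. Replace the fivefold statement with the detectable difference. For example: 50 per arm gives 80% power for a between-arm difference of about 5.7 points if the SD is 10 on the chosen scale, or about 6.3 points if 20% loss to follow-up is assumed. The sponsor would have to supply its own loss assumption, since the article states none. It should also say why a difference of that size is plausible.

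The cost is wording only, with no added patients and no change to conduct. The downside is that the stated margin becomes less favourable.
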